## Abstract

**Background:**

Sarcopenia is an age-associated disorder characterized by a progressive decline in skeletal muscle mass, strength, and physical function. The condition is linked to low levels of anabolic hormones such as insulin-like growth factor 1 (IGF-1), with its downstream phosphatidylinositol 3 kinase (PI3K)/ protein kinase B (AKT)/ forkhead box protein O3 (FOXO3) signaling pathway. There is growing evidence that resistance training (RT) or vibration training (VT) could improve physical functioning in individuals with sarcopenia. However, the related physiological influence of exercise on sarcopenia remains elusive.

**Method:**

This prospective randomized controlled trial will be conducted among 96 participants, aged between 65 and 80 years. In participants, sarcopenia diagnosis will be confirmed based on the Asian Working Group for Sarcopenia criteria, and participants will be randomized into either control, RT, VT, or RVT (combined RT and VT) groups. The intervention will last 12 weeks, with assessments performed at baseline, 12 weeks (after intervention), and 24 weeks (follow-up). The primary outcomes will include skeletal muscle mass, handgrip strength, and gait speed. Secondary outcomes comprise IGF-1 concentrations, PI3K/AKT and FOXO3 protein activity, quality of life, and timed-up-and-go test performance assessments.

**Discussion:**

This clinical study aims to elucidate the potential modulation of molecular mechanisms in vivo for combined RT and VT in sarcopenia patients and to identify the effects of the intervention on physical function.

**Trial registration:**

ChiCTR, ChiCTR2400083643. Registered on April 29, 2024.

## Introduction

Sarcopenia is an age-related disorder characterized by a progressive decline in skeletal muscle mass, strength, and physical function [1]. In China, the overall prevalence of sarcopenia among community-dwelling older adults has reached 9.3%. According to the Asian Working Group for Sarcopenia (AWGS) criteria, the estimated prevalence is approximately 6.4% in men and 11.5% in women aged 60 years and above [2]. Individuals with sarcopenia could have accidental falls [3], fractures of the upper and lower limbs [4], physical disability [5], cognitive impairment [6], and poor quality of life [7], with an increased mortality risk [8]. The changes observed in older individuals with sarcopenia can have clinical and physiological impacts, such as age-related inflammation, metabolic abnormalities, and endocrine changes [9–11].

Sarcopenia has been linked to reduced levels of anabolic hormones, specifically insulin-like growth factor 1 (IGF-1), among individuals aged 60 years and above [12]. Forkhead box protein O3 (FOXO3) is a downstream component of the IGF-1 signaling pathway and is crucial for catabolic/anabolic protein homeostasis and protein breakdown within the musculoskeletal system [13]. IGF-1 activates phosphatidylinositol 3 kinase (PI3K) by binding to its receptor, which catalyzes the conversion of phosphatidylinositol-4,5-bisphosphate (PIP2), a membrane-bound molecule, to phosphatidylinositol-3,4,5-trisphosphate (PIP3), which recruits and activates protein kinase B (AKT). This, in turn, phosphorylates FOXO3 and inhibits its nuclear translocation and transcriptional activity [14]. In the anabolic state, this process decreases the expression of FOXO3’s downstream target genes (e.g., MuRF-1 and Atrogin-1 act as ubiquitin ligases and induce proteasomal degradation) and inhibits muscle protein degradation [15]. When IGF-1 signaling is diminished (e.g., owing to aging or stress), AKT activity decreases and FOXO3 dephosphorylates and enters the nucleus, stimulating an increase in MuRF-1 and Atrogin-1 levels, as well as promoting muscle atrophy *via* the ubiquitin-proteasome pathway [16–18]. Thus, a lower IGF-1 level can lead to a higher FOXO3 activity via the PI3K/AKT pathway, causing protein degradation and skeletal muscle atrophy [19], thereby resulting in the onset of sarcopenia in older adults. Among the various regulatory genes in the musculoskeletal system, FOXO3 is crucial; therefore, its inhibition might be a potential strategy for treating muscle atrophy and sarcopenia [12]. On the basis of the above evidence, it is crucial to examine the influence of different sarcopenia treatment strategies on the IGF-1/PI3K/AKT/FOXO3 pathway.

Given the absence of effective medications to specifically treat sarcopenia [20], non-pharmacological treatment remains the most promising approach to substantially enhance physical health and muscle function in older sarcopenia patients [21]. Resistance training (RT) is a widely implemented intervention for older sarcopenic adults [22]. However, RT often has high-technology requirements [23,24] and can easily produce muscle fatigue in this population [25], leading to reduced compliance with RT, especially in those who are frail. Additionally, implementing RT in clinical settings often proves challenging. Vibration training (VT), which employs platforms generating variable frequencies and amplitudes, has emerged as a potential intervention for sarcopenia in older adults [26]. Recently, VT has been increasingly employed to delay the decline in muscle function in older sarcopenia population [27–29]. A meta-analysis revealed that VT could reverse reduced muscle size, strength, and physical performance [30]. Compared with RT, the advantages of VT include being easy to perform, having short session durations, and appropriately compensating for muscle fatigue from the RT session. Wei et al. demonstrated that VT could significantly improve quadriceps voluntary activation in older sarcopenia patients [28]. Zhu et al. confirmed that tai chi combined with VT could enhance the physical function, mass, and strength of the muscles in sarcopenic men [31]. Furthermore, VT’s optimal frequency and duration can be adjusted to maximize benefits in increasing muscle size, strength, and physical performance in age-linked muscle loss patients [32,33]. Thus, combining VT with RT may offer a more effective approach for mitigating sarcopenia.

In terms of the cell signaling pathways, animal studies have shown IGF-1 pathway activation via VT [34]. Increased IGF-1 levels and improved muscle mass were also observed in sarcopenic patients after RT [35]. However, another study found no increase in inactivated FOXO3 in older women after 12 weeks of RT, implying limited benefits of RT in these women [36]. Preclinical studies have further demonstrated that vibration stimuli can promote muscle protein synthesis via mechanical loading–induced IGF-1 expression. For instance, Li et al. [34] reported that VT activated the PI3K/AKT/mTOR pathway and suppressed muscle atrophy in aged mice. Human studies have also reported increased serum IGF-1 levels following VT, suggesting systemic anabolic responses [28]. The proposed mechanism in this study is that VT enhances neuromuscular activation and mechanosensitive stimulation, which upregulates IGF-1 production. This in turn activates the PI3K/AKT signaling cascade, leading to phosphorylation of FOXO3 and reduced expression of its downstream catabolic targets, MuRF-1 and Atrogin-1. Thus, VT may shift the muscle environment toward an anabolic state through modulation of the IGF-1/PI3K/AKT/FOXO3 axis. This forms the central mechanistic hypothesis of the present protocol.

Sex-specific differences in sarcopenia are well recognized. A recent study has shown that women tend to experience a more rapid decline in muscle strength relative to muscle mass, whereas men are more likely to exhibit significant reductions in muscle mass with aging [37]. These disparities may be influenced by differences in hormonal status (e.g., estrogen vs. testosterone), muscle fiber composition, and neuromuscular control mechanisms [38]. Additionally, evidence suggests that men and women may respond differently to exercise interventions such as resistance and vibration training [39,40]. Therefore, sex-specific considerations are essential when designing sarcopenia-related interventions and interpreting outcomes.

In this study, we investigate the impact of RT combined with VT on the IGF-1/PI3K/AKT/FOXO3 axis in patients with sarcopenia. Using a single-blind randomized controlled trial, we will assess whether this combined exercise therapy exerts significant molecular and functional effects, while also exploring potential differences in treatment response between sexes.

## Methods and analysis

### Study design and grouping

This randomized controlled trial will identify the effects of RT combined with VT on the IGF-1/PI3K/AKT/FOXO3 axis in a population with sarcopenia. Participants will be screened for sarcopenia, as defined by the AWGS in 2019, and recruited based on eligibility criteria. Fig 1 summarizes the participant’s enrollment process, interventions, and assessment schedule. Once informed consent is received, the participants will be randomly categorized into (1) control, (2) RT, (3) VT, and (4) combined RT and VT (RVT) groups. Intervention will last 12 weeks, with data collection and assessments at baseline, 12-week (after intervention), and 24-week (follow-up). The 12-week intervention duration was selected based on existing literature indicating that this time frame is sufficient to induce meaningful improvements in muscle mass, muscle strength, and molecular signaling among older adults. Prior studies on resistance and vibration training for sarcopenia typically range between 8–12 weeks, with 12 weeks allowing both early neural adaptation and later-stage hypertrophy to manifest [41–43]. The 24-week time point (i.e., 12weeks post-intervention) was included to evaluate the sustainability of training-induced benefits. Similar follow-up durations have been adopted in previous sarcopenia trials to assess the persistence or decay of functional gains after supervised training ends [44]. Muscle strength, mass, physical performance, FOXO3 protein expression levels, and quality of life will be assessed in all participants. Fig 2 depicts the study design, and S1 File contains the SPIRIT checklist.

**Fig 1 pone.0333343.g001:**
[figure not shown]
Enrollment, interventions, and assessments schedule. RT: resistance training, VT: vibration training, RVT: resistance training combined with vibration training, IGF-1: insulin-like growth factor 1, PI3K/AKT: phosphatidylinositol 3-kinase/ protein kinase B, FOXO3: forkhead box protein O3, SF-36: 36-item short form health survey.

**Fig 2 pone.0333343.g002:**
[figure not shown]
Study flow chart. RT: resistance training, VT: vibration training, RVT: resistance training combined with vibration training, IGF-1: insulin-like growth factor 1, PI3K/AKT: phosphatidylinositol 3-kinase/ protein kinase B, FOXO3: forkhead box protein O3, SF-36: 36-item short form health survey.

### Sample size determination

The required sample size was calculated using G*Power (version 3.1.9.7, Germany) for a two-way repeated-measures ANOVA (within-between interaction), with a significance level of α = 0.05, power (1–β) = 0.80, and four intervention groups (Control, RT, VT, RVT). The effect size was set to f = 0.40 (partial η^2^ = 0.14), which reflects a moderate-to-large effect based on prior studies assessing changes in IGF-1 expression and physical function following resistance and vibration training in older adults. The primary endpoint for power estimation was the change from baseline to 12 weeks, representing the completion of the supervised intervention. The 24-week point is considered a follow-up to assess sustainability but was not included in the power calculation. Considering a 20% dropout rate, the minimum required sample size was estimated at 73 participants [45]. Therefore, we plan to recruit 96 individuals (24 per group) to ensure adequate statistical power. In view of multiple primary outcomes and six pairwise comparisons among four groups, Holm–Bonferroni correction will be applied to adjust for potential inflation of type I error. Additionally, the hypothesis is based on additive rather than synergistic effects between RT and VT. Hence, interaction effects were not included in the sample size model but will be explored post hoc.

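### The stated minimum of 73 is the number needed before dropout, not after it; the inflated figure is 92 to 95, which the planned 96 just covers

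*Protocol article*

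**What the plan says.** All of this is in the protocol article, under Sample size determination. The calculation was done in G*Power "for a two-way repeated-measures ANOVA (within-between interaction), with a significance level of α = 0.05, power (1–β) = 0.80", for "four intervention groups (Control, RT, VT, RVT"). The effect size is given in two forms: "The effect size was set to f = 0.40 (partial η^2^ = 0.14"). The time span is fixed by "The primary endpoint for power estimation was the change from baseline to 12 weeks", and the 24-week visit is expressly left out of the power calculation. The result is then reported: "Considering a 20% dropout rate, the minimum required sample size was estimated at 73 participants". The next sentence sets recruitment at 96, that is 24 per group.

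The section gives no figure before dropout, no correlation between repeated measures, and no statement of how f was defined for the repeated-measures test.

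**The concern.** The sentence says that 73 already allows for a 20% loss. If so, the number needed for analysis would be about 73 × 0.8 = 58.4, and the plan to recruit 96 would carry a surplus of 96 − 73 = 23 participants.

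But 73 is a familiar result for four groups at f = 0.40 without any dropout allowance. If it is the evaluable number, the dropout clause is attached to the wrong figure and the surplus does not exist. Recruitment is still open according to the section on trial registration and status, so anyone judging whether enrolment is sufficient should know which of the two is meant.

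**Working it through.** **Inputs, all from Sample size determination.** k = 4 groups; f = 0.40, so f² = 0.16; alpha = 0.05; power = 0.80; m = 2 time points (baseline and 12 weeks); dropout 20%. The correlation rho between the two time points is not stated, so it is varied. Power is taken from the noncentral F distribution with noncentrality λ. Dropout is applied as N / (1 − 0.20).

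**Step 1. Where 73 comes from.** For a one-way comparison of the four groups on change, λ = f² × N with 3 and N − 4 degrees of freedom.

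- N = 72: λ = 0.16 × 72 = 11.52, power 0.799.
- N = 73: λ = 0.16 × 73 = 11.68, power 0.805.

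So 73 is the first total to reach 80%, with no dropout in the calculation. Equal groups need 76 (power 0.823).

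**Step 2. The test named in the protocol can give the same number.** For the within-between interaction with f read from partial eta-squared (the Cohen option in G*Power), λ = f² × N × (m − 1), with (k − 1)(m − 1) and (N − k)(m − 1) degrees of freedom. With m = 2 this is λ = f² × N on 3 and N − 4, which is the test in Step 1, so it also gives 73. The SPSS option, λ = f² × (N − k) × (m − 1), gives 76.

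**Step 3. Add the dropout.**

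- 73 / 0.8 = 91.25, so 92.
- 76 / 0.8 = 95. The next multiple of four is 96, the planned total.

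**Step 4. Does the G*Power default option give 73 with dropout included?** Here λ = f² × N × m / (1 − rho), on 3 and N − 4 degrees of freedom.

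| rho | evaluable N | after 20% dropout |
|---|---|---|
| 0.5 | 22 | 28 |
| 0.3 | 29 | 37 |
| 0 | 39 | 49 |
| −0.55 | 57 | 72 |
| −0.6 | 59 | 74 |

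Rounding to equal groups changes the first three rows to 24, 32 and 40 evaluable, or 30, 40 and 50 after dropout. A total near 73 needs rho of about −0.55 to −0.6, which is implausible for two measurements on the same person.

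**Step 5. Other routes to a dropout-inclusive 73.** Two were found, and each changes something the protocol states. One is the default interaction at rho = 0 with power 0.95 in place of 0.80 (58, then 58 / 0.8 = 72.5, so 73). The other is the between-factors test with rho about 0.57 (58, then 73).

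**Step 6. Small check on f.** Partial eta-squared of 0.14 converts to f = √(0.14 / 0.86) = 0.403. With that value the one-way test needs 72, or 72 / 0.8 = 90 after dropout. The conclusion is unchanged.

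**Step 7. What the planned 96 delivers.** 96 × 0.8 = 76.8 evaluable. Power is 0.828 on the calculation of Steps 1 and 2, and 0.805 under the SPSS option. Both are for one omnibus test at alpha 0.05.

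**Step 8. What 73 enrolled would deliver.** 73 × 0.8 = 58.4, so 58 evaluable. Power is 0.691 on the calculation of Steps 1 and 2, 0.656 under the SPSS option, and 0.951 (rho = 0) to above 0.999 (rho = 0.5) under the G*Power default.

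**The case against.** The best defence is that nothing in the conduct of the trial depends on this sentence. The article fixes enrolment at 96 in the abstract, the sample size section and the randomization section, and nowhere allows recruitment to stop at 73. After a 20% loss, 96 still leaves more than the 73 or 76 needed. That stands, and it makes this a correction of reporting rather than a fault in the size of the trial.

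Two stronger readings are tempting, and the article does not support either.

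- A reader might infer that the wrong test was used, because the default interaction formula gives far smaller numbers than 73. Step 2 shows that the named "two-way repeated-measures ANOVA (within-between interaction") gives 73 when f is taken from partial eta-squared, and the section does tie f to that quantity. A between-group calculation is one possible origin of 73, not an established one.
- A reader might infer that the trial has 69% power. That figure needs two conditions together: enrolment of only 73, and the effect-size reading of Steps 1 and 2. The first is not planned. Without the second, 58 evaluable gives 95% or more at any correlation of zero or above.

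The defence does not rescue the sentence itself. The dropout step is not something left to a fuller document: it is stated, and it is attached to a number that does not contain it.

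**Conclusion.** The statement that 73 includes a 20% dropout allowance is wrong under the stated inputs. At f = 0.40, 73 is the evaluable number; the figure with dropout is 92, or 95 in equal groups, an understatement of 19 to 22 participants (92 − 73 and 95 − 73).

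The target of 96 remains adequate for the stated 80% power. Its margin is thin: about 77 evaluable against 73 to 76 needed, with power of about 83%, or about 80.5% under the SPSS option. As printed, the paragraph makes 96 look like 23 more than needed.

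These powers rest on f = 0.40, a loss of exactly 20%, and a single omnibus test at unadjusted 0.05. They make no allowance for the Holm–Bonferroni correction that the same section announces for several primary outcomes and six pairwise comparisons.

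**What to change.** Restate the paragraph along these lines: for the baseline to 12-week comparison of four groups with f = 0.40, alpha 0.05 and power 0.80, 73 evaluable participants are needed (76 in equal groups); allowing for 20% dropout this becomes 92 (95 in equal groups), rounded to 96, or 24 per group.

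State which effect-size option was used in G*Power and, if that option uses one, the assumed correlation between baseline and 12 weeks. If the default option with a correlation was really intended, report the number that it yields in place of 73.

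The cost is the rewording of one paragraph. Enrolment, allocation and analysis do not change.

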### Inclusion criteria

The inclusion criteria are as follows: 1) individuals between age 65 and 80 years; 2) sarcopenia diagnosis based on the AWGS 2019 criteria: appendicular skeletal muscle mass index < 7.0 and < 5.7 kg/m^2^ for men and women, respectively, using a bioelectrical impedance analyzer, handgrip strength < 28 and < 18 kg in men and women, respectively, and/or gait speed < 1.0 m/s in the 6-meter walk test; 3) not regularly exercising for > 3 months; 4) willingness to participate voluntarily and sign the informed consent form for this trial.

### Exclusion criteria

The exclusion parameters included individuals with: 1) uncontrolled hypertension, hyperlipidemia, or diabetes mellitus; 2) untreated gallstones, kidney stones, or infectious diseases; 3) pathological bone diseases or chronic inflammatory diseases (e.g., rheumatoid arthritis); 4) any disorders that limit the ability to complete the required exercises in the study; 5) cardiovascular disease requiring a pacemaker or having a malignant tumor; 6) acute fractures or severe osteoarthritis; 7) current use of medications known to affect muscle metabolism or hormonal balance, including but not limited to systemic corticosteroids, anabolic steroids, or hormone replacement therapy. Additionally, all participants’ current use of medications for cardiovascular or metabolic conditions (e.g., beta-blockers, statins, insulin sensitizers) will be documented at baseline. If imbalances between groups are identified, these variables will be considered as covariates in the statistical analysis; 8) current or recent (within the past 3 months) use of nutritional supplements that may affect muscle metabolism or sarcopenia progression, such as protein powders, amino acids, vitamin D, or calcium supplements.

### Recruitment strategy

Potential participants will be recruited through educational seminars at partner community centers, promotional materials distributed both onsite and online, and referrals from collaborating organizations. Screening will investigate handgrip strength, bioelectrical impedance, and gait speed based on the AWGS 2019 criteria. Eligible individuals will receive invitations to participate in the study at Sichuan Province’s Sports Medicine Key Laboratory. Prior to enrollment and during the informed consent process, all participants will be informed about the study procedures, as well as the potential risks and benefits. Participants will retain the right to withdraw unconditionally at any stage of the research.

### Randomization and blinding

After acquiring the signed consent forms, 96 participants will be screened for eligibility and will be randomly categorized into the RT, VT, RVT, or control group, at a 1: 1: 1: 1 ratio using computer-generated simple randomization. A reproducible random number sequence will be generated using IBM SPSS (version 27.0), and participants will be sorted in ascending order based on these numbers. Group allocation will be determined using a modulo-4 method: remainder 0 = RT, remainder 1 = VT, remainder 2 = RVT, and remainder 3 = control, ensuring equal group sizes. No baseline characteristics (e.g., age, sex) will be used as stratification factors during randomization. To minimize allocation bias, group assignments will be concealed using sequentially numbered, opaque, sealed envelopes (SNOSE), and only personnel responsible for randomization will have access to the sequence. Investigators, outcome assessors, and statisticians will remain blinded to group allocation throughout the study.

### Interventions

#### Group protocols.

Participants in the RT, VT, and RVT groups will undergo pre-training to acquaint them with the respective protocols before commencing formal training. Before and after each treatment session, participants in the three intervention groups will complete a 5-minute warm-up and cool-down. All training sessions will be conducted in a group under the guidance of professional physiotherapists. Throughout the training period, participant attendance and adherence will be systematically documented. If a participant cannot start the training session on time for any reason, they can join training sessions that will be carried out at other times during that week. All participants will be asked to refrain from engaging in any additional physical activity and maintain their usual daily habits throughout the study.

